### **Adverse events**

Adverse events will be observed through a non-leading questionnaire (Appendix G) throughout the entire phase of the intervention, as an element of the participant's training diary. Participants are welcome to contact the PI and the relevant physiotherapist(s) whenever necessary throughout the study period. Any adverse events or harm to participants during the intervention will be communicated to the principal investigator daily. We intend to disclose and publish the findings, regardless of their outcome.

## Sample Size

Sample size calculations are performed using SPSS version 29 for the primary outcome: differences between two means of Hamstring MVIC peak force symmetry index (see Figure 11). With the population standard deviation for the main outcome measure amount of 0.71 as in the Harput et al. study, type I error of 0.05, type II error of 0.2, 80% power, the minimum sample size required is 14 patients per group (28 in total). Expecting an attrition rate of 10%, 16 participants are considered for each study group.

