## **S1 Appendix. Study Protocol for Ethics Application**

### **EFFECT OF UPPER LIMB ISOMETRIC TRAINING ON HAMSTRING STRENGTH IN EARLY POSTOPERATIVE ANTERIOR CRUCIATE LIGAMENT RECONSTRUCTION PATIENTS: A RANDOMISED CONTROLLED TRIAL**

#### **Abstract**

This study aims to investigate the effects of upper limb isometric training (ULIT) combined with standard care of an anterior cruciate ligament reconstruction (ACLR) rehabilitation program on hamstring strength and physical function in the early-phase postoperative period. Early recovery of hamstring strength is critical for knee stability and functional rehabilitation post-ACL surgery. Hamstring strength deficits are prolonged issues in rehabilitation, with significant hamstring strength deficiencies in an early postoperative ACLR, especially using hamstring autograft, leading to functional limitations and an increased risk of secondary injuries. High knee muscle strength imbalances can hinder strength return in later stages. However, swelling, donor site pain, joint stiffness, and graft protection often neglect the direct activation of the hamstring in the early period. Also, clinical practice guidelines and consensus on early rehabilitation strategies are conflicting. While lower limb strengthening exercises are the mainstay of rehabilitation, this study explores the potential benefits of ULIT in promoting hamstring activation through the inter-limb posterior myofascial kinetic chain. This study hypothesise that participants receiving ULIT in addition to standard care will demonstrate better hamstring strength at 12 weeks post-operatively compared to those receiving standard care rehabilitation alone. A total of 32 patients who underwent ACLR with hamstring tendon autografts will be randomly assigned to either the ULIT group or a control group. The ULIT group performed upper limb isometric exercises in addition to standard postoperative rehabilitation, while the control group followed the standard rehabilitation protocol alone. We will measure hamstring and quadriceps strength using hand-held dynamometry at baseline (preoperative), 4, 8, and 12 weeks postoperatively. The primary outcome is the change in hamstring strength in the operated limb, while secondary outcomes included hamstring flexibility and patient-reported outcomes on symptoms, physical function and adherence. Statistical analysis will be conducted to compare the strength recovery between the two groups. It is believed that the results of this study will enhance knowledge about the global functional muscle concept, offer effective, safe, inexpensive, and feasible interventions, and promote further research on the interlimb connection of muscle activation and flexibility in heterologous muscle groups after ACLR.

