## **Specific Objectives**

1. To investigate the difference in hamstring strength between the ULIT and the standard care group compared to the standard care alone group at 4, 8, and 12 weeks post-ACLR.
2. To measure the changes in physical function based on the IKDC score in the ULIT group compared to the standard care group at preoperative and 12 weeks post-ACLR.
3. To evaluate the effect of ULIT on hamstring flexibility, measured by the active knee extension test (AKET) test, compared to standard care alone at preoperative and 12 weeks post-ACLR.
4. To analyse the relationship between patient adherence to ULIT and improvements in hamstring strength and physical function over the 12-week rehabilitation period.

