## **Research Hypothesis**

We hypothesise that participants receiving the ULIT plus standard care will have better hamstring strength at 12 weeks post-operatively compared to participants receiving a standard care rehabilitation program alone.

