### **Data Collection**

The study will collect demographic data, as well as pre-, intra-, and postoperative data (see Table 3). Data will be gathered from the participants and their medical records for all the data collection forms (see Appendix A, C, and D). Baseline evaluations will be conducted throughout the pre-operative period, within a range of 14 days, to reduce any bias when selecting participants. The subsequent assessment in the 4th week ( $\pm 14$  days), 8 weeks ( $\pm 14$  days), and three months ( $\pm 14$  days) are scheduled at the Orthopaedic Clinic (van Melick et al., 2021). The blinded assessors will give all tests and questionnaires in person, ensuring participant consistency. These assessments will take place at four weeks, eight weeks and three months after the surgery. Phone consultations will be used for post-hospital discharge follow-up. Participants who cannot be reached by phone for a continuous period of 14 days starting from the assessment due date will be classified as lost to follow-up for outcome measurement.

intra-reliability had a value of 0.9269 [95% C.I.: 0.8909–0.9533] (Grgic et al., 2020; Karagiannopoulos et al., 2022; Romero-Franco et al., 2019).

The participants are directed to generate deliberate isometric contractions of their quadriceps or hamstring muscles, by pushing against the resistance provided by the dynamometer's arm with a perceived maximal effort of 100% (Grgic et al., 2020). During the formal testing, the participants conducted three maximum voluntary isometric contractions (MVIC) of knee extension lasting five seconds each for the quadriceps (Padulo et al., 2020). Similarly, This is followed by knee flexion testing for the hamstrings. A minute rest time will be given between the quadriceps and hamstring testing (Mellemkjær et al., 2024).

The assessor will consistently give instruction and verbal encouragement (see Appendix I). The participants are instructed to exert maximum force by either pushing with their quadriceps or pulling with their hamstrings against the dynamometer. The average and best scores of the peak forces will be recorded (Grgic et al., 2020).

The average scores of quadriceps and hamstring muscular strength during rehabilitation are quantified using the Quadriceps Index (QI) and Hamstring Index (HI), which are calculated using the formula:  $(\text{MVIC peak force of the affected limb} / \text{MVIC peak force of the unaffected limb}) \times 100$  (van Melick et al., 2021).

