## Statistical Analysis

The data analysis will be conducted using the SPSS Windows Version 29.0 software (SPSS, Chicago, IL, USA). The data will be summarised using descriptive statistics such as the mean and standard deviation, median and interquartile range, quantity and percentage, and frequency, depending on the distribution and type of data. This encompasses participant demographics as well as adherence to exercise. To evaluate the normality of the data, we will examine the skewness and kurtosis statistics (the ratio of the statistic to the standard error) by conducting the Shapiro-Wilk test. Boxplots are employed to detect outliers.

The main outcome measure, the mean changes in hamstring isometric peak force between 4 and 12 weeks, will be assessed using a paired t-test. The main hypothesis will be tested by comparing the changes in the mean difference between the intervention group and the standard

care group. The missing data will be analysed according to the intention-to-treat concept, considering the groups to which participants have been randomly allocated. Descriptive analysis, on the other hand, will describe missing data patterns in great detail to look for possible biases. If the data distribution exhibits non-normality or ceiling/floor effects, a non-parametric test (specifically, the Mann-Whitney test) will be conducted. Furthermore, this study will employ one-way repeated-measures ANOVA within-group measurements to investigate potential differences between the Quadriceps Index and Hamstring Index over an interval of time.

The secondary outcome data, which includes measurements of hamstring flexibility, range of motion, IKDC scores, and exercise adherence, will be summarised and evaluated in a manner consistent with the primary result. A repeated measures analysis of variance (ANOVA) will be used to examine the impact of rehabilitation and time on all the measured variables.

Statistical significance will be determined by a p-value of less than 0.05 (two-tailed) for all conducted tests with a 95% confidence interval.

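### The protocol names incompatible primary outcomes (symmetry index, 4-to-12-week change in force, 12-week strength), and its power statement does not fit the outcome it was written for

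*Protocol*

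**What the plan says.** Protocol, Sample Size: the calculation is for the "primary outcome: differences between two means of Hamstring MVIC peak force symmetry index". It uses an SD of 0.71 credited to a cited cohort, type I error 0.05 and 80% power. It arrives at 14 per group, raised to 16 for 10% attrition. The reproduced source table (Table 1) gives peak torque in Nm/kg.

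Protocol, Statistical Analysis: "The main outcome measure, the mean changes in hamstring isometric peak force between 4 and 12 weeks, will be assessed using a paired t-test". A between-group comparison of these changes is then to serve as the test of the main hypothesis. The Quadriceps and Hamstring Indices get their own one-way repeated-measures ANOVA within groups.

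Protocol, Research Hypothesis: participants given upper limb isometric training (ULIT) "will have better hamstring strength at 12 weeks post-operatively".

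Protocol, Abstract: "The primary outcome is the change in hamstring strength in the operated limb", with no start or end visit in that sentence.

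Protocol, Specific Objectives, item 1: a group difference in strength "compared to the standard care alone group at 4, 8, and 12 weeks post-ACLR", with no visit put first.

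Protocol, Data Collection: "The average and best scores of the peak forces will be recorded". The index is the affected limb divided by the unaffected limb, times 100, and is tied to the average score.

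**The concern.** A confirmatory trial needs one primary quantity: one limb or ratio, one scale, one visit or interval, one contrast. Here the section that sets the number of patients uses a ratio of two limbs, and the section that tests the hypothesis uses a change in force. The hypothesis speaks of a level at one visit. A result on one need not carry over to another.

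Two things are at stake. First, power: a sample size holds only for the outcome whose difference and SD went into it. Second, error control: if the choice is still open when the data are seen, the 5% level no longer describes the chance of a false claim.

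**Working it through.** **Inputs.** From Sample Size and Statistical Analysis: SD 0.71, two-sided alpha 0.05, power 80%, 14 per group, 10% attrition. From Table 1, hamstring torque in Nm/kg: operated limb 1.0 ± 0.5, 1.32 ± 0.9 and 1.55 ± 0.8 at 4, 8 and 12 weeks; other limb 1.86 ± 0.34, 1.89 ± 0.46 and 2.05 ± 0.38. All correlations below are assumptions, because the protocol gives none.

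**1. The plan's own figure.** The attrition step reproduces: 14 / 0.90 = 15.6, rounded up to 16. The 14 cannot be reproduced, because no difference to detect is stated. Solving backwards:

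- Normal formula: difference = SD × (1.960 + 0.842) × √(2/14) = 0.71 × 2.802 × 0.378 = 0.75, which is 1.06 SD.
- Two-sample t-test: 0.78, which is 1.10 SD.

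**2. Which scale does 0.71 fit?** It is not one of the SDs printed in Table 1. The SD of a 4-to-12-week change in operated-limb torque is √(0.5² + 0.8² − 2r × 0.5 × 0.8) = √(0.89 − 0.8r). With r = 0.5 this is 0.70; with r = 0.48 it is 0.71. So 0.71 is natural for a change in Nm/kg.

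The index from the table means is:

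- week 4: 1.0/1.86 = 53.8%
- week 8: 1.32/1.89 = 69.8%
- week 12: 1.55/2.05 = 75.6%

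Read as a ratio, an SD of 0.71 is 71 percentage points, and the implied difference is 75 to 78 points, as large as the whole 12-week index. Read on the ×100 scale, it is 0.71 of a point. Neither is plausible. The delta method gives an approximate SD for the 12-week index:

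0.756 × √(0.516² + 0.185² − 2ρ × 0.516 × 0.185), where 0.516 = 0.8/1.55 and 0.185 = 0.38/2.05.

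This is 41 points at between-limb correlation ρ = 0 and 31 points at ρ = 0.7. With 14 per group, 80% power then needs a true difference of about 44 or 33 points (SD × 2.802 × 0.378).

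**3. Sensitivity of the number.** If the table's own 4-to-12-week gain, 1.55 − 1.0 = 0.55 Nm/kg, were taken as the between-group difference (an assumption) with SD 0.71, a two-group comparison needs 27 (normal) or 28 (t-test) per group before attrition.

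**4. Cost of an open choice.** A simulation under no effect used 14 per arm, Table 1 means and SDs, correlations over time of 0.3 to 0.7 and between limbs of 0.3 to 0.6. Four versions were tested: 12-week force, 4-to-12-week change in force, 12-week index, and change in index.

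- At least one of the four with p < 0.05: 10.7% to 11.1%.
- At least one of the two force versions: 7.6% to 8.1%.
- One fixed outcome: 5%.

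Four independent tests would give 1 − 0.95⁴ = 18.5%, an upper reference only.

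**5. What the index does if both legs respond.** Start from 75.6% and suppose ULIT raises the operated limb by 20% (0.31 Nm/kg). The index rises by:

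- 75.6 × 1.20 − 75.6 = 15.1 points if the other limb is unchanged
- 75.6 × 1.20/1.10 − 75.6 = 6.9 points if the other limb gains 10%
- 0 if the other limb also gains 20%

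**The case against.** The best defence is that Statistical Analysis does name a single main measure and says the main hypothesis is tested by comparing changes between groups. On that reading the Abstract's operated-limb change is the same outcome with less detail, item 1 of the Specific Objectives names no primary, and the hypothesis is loosely worded. Part of this stands: the Abstract and the analysis are compatible, and the objective is not a rival primary. The index remains, because Sample Size calls it primary while the analysis handles it separately. So does the gap between a 12-week level and a change.

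The strength-testing text in Data Collection begins mid-sentence in the copy at hand, so a paragraph defining the primary outcome may have been lost. That could add a definition, but it would not reconcile the sections quoted above. It is a reason not to press the average-versus-best question far.

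Some stronger readings are tempting but unsupported:

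- **Twelve candidate primaries** (force or index, three reference points, average or best). Data Collection ties the index to average scores, and no section states change from the preoperative visit as the primary.
- **A false-positive rate of 11-14% from three visits.** This treats weeks 4, 8 and 12 as co-primary, which the analysis section does not do.
- **The index hides a true effect.** Full cancellation needs an equal proportional gain in the other leg. The inter-limb rationale makes some gain conceivable but does not establish it. Table 1 does show the other limb rising from 1.86 to 2.05 (10%), but that is recovery over time, which both arms would share, and not a treatment effect.
- **The 14 came from a paired formula.** A paired normal formula with 0.55 and 0.71 gives 13.08, which rounds up to 14. The protocol does not say which route was taken.

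**Conclusion.** The contradiction is in the current text and should be resolved before unblinding. An index, a change in force and a 12-week level are each put forward as what the trial is about, and only the index is attached to the sample size. The SD behind that sample size belongs, as far as can be told, to torque in Nm/kg. The claim of 80% power with 14 per group is therefore unsupported for the index. On any scale where 0.71 is the right SD, it rests on an unstated difference of about 1.1 SD.

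The error inflation, roughly 8-11% against 5%, is a risk that arises only if the choice is made after the data are seen. It depends on the assumed correlations. The protocol does not plan such a choice, and a reader should not infer one. Attenuation in the index is likewise conditional on a ULIT gain in the uninvolved leg.

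**What to change.** Name one primary outcome and use it everywhere. One workable choice is operated-limb hamstring MVIC at 12 weeks, average score, compared between groups with adjustment for the preoperative value. Make the Hamstring Index, the 4-to-12-week change, week 8 and the best score secondary.

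Do not treat week 4 as an efficacy comparison, since ULIT starts in the fourth week. Do not use it as the adjusting covariate either: the visit follows randomisation, and its ±14-day window can fall after ULIT has begun. The preoperative value precedes randomisation and is safe.

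Restate the assumed difference, SD and resulting power on the chosen scale. If that scale is force, or force per kg, the Nm/kg figures in Table 1 do not transfer directly, because torque also needs a lever arm. Align the Abstract, Research Hypothesis, Specific Objectives, Sample Size and Statistical Analysis.

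The cost is mainly wording, plus a search for an SD on the right scale; the outcome measurements are already planned. The downside is that the restated power may look worse. As a guide, with Table 1's 12-week SD of 0.8 Nm/kg and no adjustment, 14 per group has 80% power for 0.8 × 1.06 to 0.8 × 1.10 = 0.85 to 0.88 Nm/kg. That is about 55-57% of the operated-limb mean of 1.55. Adjustment would improve on this to an extent the protocol gives no basis to estimate.

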## **Randomisation and Allocation**

Following the baseline assessments, individuals will be assigned either to the intervention group or the control group by a simple random sampling. The randomisation process will be performed using a computer-generated sequence numbering scheme ranging from one (1) to thirty-two (32), with an equal allocation ratio of 1:1. The concealment is achieved using a set of sealed and numbered envelopes. Allocation takes place following baseline testing (T1), when a staff of the Orthopaedic Department, who is not participating in the study, opens the next study envelope. Subsequently, they notify the group assignment to the attending physiotherapist. The envelopes will be securely stored and sealed in a cabinet to ensure security and prevent any unauthorised access. Measures will be implemented to restrict the number of authorised individuals who have access or authority to open the research envelopes, to prevent any potential bias in the allocation process. The statistical analysis will specifically focus on allocation codes, ensuring that the data analyzers remain unaware of the study group allocation (see Figure 9).

[figure not shown]

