**Table 1 Hamstring and Quadriceps Muscle Strength Outcomes at 4, 8, and 12 Weeks, Mean  $\pm$  SD**

| Muscle                         | Limb       | Time Point       |                  |                  | P     |
|--------------------------------|------------|------------------|------------------|------------------|-------|
|                                |            | 4 wk             | 8 wk             | 12 wk            |       |
| Hamstring peak torque (Nm/kg)  | Involved   | 1.0 $\pm$ 0.5*   | 1.32 $\pm$ 0.9*  | 1.55 $\pm$ 0.8*  | <.001 |
|                                | Uninvolved | 1.86 $\pm$ 0.34† | 1.89 $\pm$ 0.46  | 2.05 $\pm$ 0.38† | .001  |
| Quadriceps peak torque (Nm/kg) | Involved   | 1.47 $\pm$ 0.62* | 2.18 $\pm$ 0.65* | 2.61 $\pm$ 0.67* | .001  |
|                                | Uninvolved | 2.60 $\pm$ 0.63* | 2.88 $\pm$ 0.73* | 3.14 $\pm$ 0.64* | .001  |

\*Quadriceps and hamstrings peak torques were significantly different between the 4th, 8th, and 12th weeks for the involved limb, and quadriceps peak torque was significantly different between the 4th, 8th, and 12th weeks for the uninvolved limb. †Significant difference for hamstrings peak torque between the 4th and 12th weeks for the uninvolved limb.

**Figure 11:** Sample size for the RCT based on the study by Harput (2015)

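### The 80% power claim for 14 per group is unsupported: no target difference is stated, the SD of 0.71 cannot be traced, and the sized outcome is neither the tabulated nor the analysed one

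*Protocol*

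**What the plan says.** The Sample Size section sizes the trial on "differences between two means of Hamstring MVIC peak force symmetry index". The inputs follow: "With the population standard deviation for the main outcome measure amount of 0.71 as in the Harput et al. study", then "type I error of 0.05, type II error of 0.2, 80% power". The result is that "the minimum sample size required is 14 patients per group (28 in total", raised to 16 per group for 10% attrition. No target difference appears there or elsewhere in the protocol.

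Table 1, captioned as the basis for the sample size, gives "Hamstring peak torque (Nm/kg" by limb at 4, 8 and 12 weeks. For the operated limb it shows 1.0 (SD 0.5), 1.32 (SD 0.9) and 1.55 (SD 0.8). For the other limb it shows 1.86 (SD 0.34), 1.89 (SD 0.46) and 2.05 (SD 0.38).

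The Statistical Analysis section states: "The main outcome measure, the mean changes in hamstring isometric peak force between 4 and 12 weeks, will be assessed using a paired t-test". It then says that the main hypothesis rests on comparing those changes between the two groups. It fixes the test level: "Statistical significance will be determined by a p-value of less than 0.05 (two-tailed". The Randomisation and Allocation section sets two groups "with an equal allocation ratio of 1:1".

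**The concern.** A power statement links four things: sample size, SD, error rates and the difference to be detected. With the difference missing, 80% power has no content, and a reader cannot tell what effect the trial was built to find.

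The SD adds a second difficulty. It has no unit and cannot be found in the table offered as its source. Three different quantities are also in play: torque in the table, a limb symmetry index in the calculation, and a change in force in the analysis. An SD for one of these does not carry over to another.

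This paragraph is the only justification for enrolling 32 patients. If the 80% figure is taken at face value, a non-significant result could be given more weight than the design supports.

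**Working it through.** **Inputs.** From Sample Size: SD 0.71, alpha 0.05, power 0.80, n = 14 per group, attrition 10%. From Statistical Analysis: two-sided. From Randomisation and Allocation: 1:1. From Table 1: operated hamstring 1.0 (SD 0.5) at week 4 and 1.55 (SD 0.8) at week 12, a gain of 1.55 − 1.0 = 0.55 Nm/kg.

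**1. Can the plan's 14 be reproduced?** No. The two-sample formula n = 2(z₀.₉₇₅ + z₀.₈₀)² SD²/δ² needs δ, and none is given. The attrition step does reproduce: 14/0.9 = 15.6, rounded up to 16.

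**2. What 14 per group can detect.** Solving the two-sided two-sample t-test (noncentral t, 26 df) for 80% power gives d = 1.10. The normal approximation gives 2.802 × √(2/14) = 1.06. With 16 per group the t-test gives d = 1.02. These values do not depend on any SD.

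**3. If 0.71 is the per-group SD in Nm/kg.**
- Detectable difference at n = 14: 1.10 × 0.71 = 0.78 Nm/kg. At n = 16: 1.024 × 0.71 = 0.73 Nm/kg.
- Table 1's whole operated-limb gain from week 4 to week 12 is 0.55 Nm/kg.
- Power for 0.55 (d = 0.55/0.71 = 0.775): 51% at n = 14 and 56% at n = 16.
- Power at n = 14 for smaller differences: 43% for 0.50, 30% for 0.40 and 19% for 0.30.

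**4. If the SD of change is built from Table 1.** The analysed outcome is a change, so its SD is √(0.5² + 0.8² − 2r × 0.5 × 0.8) = √(0.89 − 0.80r), where r is the correlation between weeks 4 and 12. The protocol does not give r, so the values below are assumptions.

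| r | SD of change | Detectable difference, n = 14 | Power for 0.55, n = 14 |
|---|---|---|---|
| 0 | 0.943 | 1.04 | 32% |
| 0.5 | 0.700 | 0.77 | 52% |
| 0.7 | 0.574 | 0.63 | 68% |
| 0.8 | 0.500 | 0.55 | 80% |

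**5. If 0.71 is on the index scale, as a ratio.** The ratio of Table 1 means is 1.0/1.86 = 0.54 at week 4 and 1.55/2.05 = 0.76 at week 12, a rise of 0.22. The detectable difference would again be 0.78.

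**6. Precision.** The expected half-width of the 95% confidence interval for the group difference at n = 14 is t₀.₉₇₅,₂₆ × √(2/14) × SD = 2.056 × 0.378 × SD = 0.78 SD. At SD 0.71 that is 0.55 Nm/kg.

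**The case against.** The strongest reply is that the power figures depend on what 0.71 means, and the protocol does not say. That is right. A two-sample t-test with a difference of 0.55 and a per-group SD of 0.5 (Table 1, operated limb, week 4) needs 14.0 per group. Moreover, 0.5 × √2 = 0.707, so 0.71 could be the SD of a difference between two such values. On that reading, 14 per group would be a sound between-group calculation for 0.55 Nm/kg. Against it, the section calls 0.71 the population SD of the main outcome, and Table 1's SDs at weeks 8 and 12 are larger. Still, it cannot be excluded.

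A reader might infer that a within-group formula was used, because 7.849 × (0.71/0.55)² = 13.08 rounds up to 14 and the analysis section mentions a paired test. The documents do not establish this. The SD 0.5 reading fits equally well, and 0.71 is also close to an SD of change at r of about 0.48. How 14 arose cannot be determined.

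A reader might also infer that the trial cannot detect any plausible benefit. Table 1 compares limbs and time points, not treatments. It gives a sense of scale but sets no upper limit on a treatment effect, and it does not supply the SD of force measured by hand-held dynamometry.

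Nor does anything in the protocol say that a null result will be read as absence of effect. It plans 95% confidence intervals and publication whatever the findings. The outcome mismatch is limited to what is visible, since part of the measurement text under Data Collection is missing from the copy reviewed.

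None of this supplies the missing difference or a derivation of 0.71.

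**Conclusion.** The point holds: the protocol does not support 80% power with 14 per group. Three facts need no assumption. No target difference is given, 0.71 has no unit and is not in the cited table, and the tabulated, sized and analysed outcomes differ.

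It also follows, for a two-sided two-sample t-test, that 14 per group reaches 80% power only at d = 1.10 (1.02 if all 16 are evaluable). The rest is conditional. Taking 0.71 as a per-group SD in Nm/kg, which the section's wording suggests, the detectable difference is 0.78 Nm/kg and power for 0.55 is 51%. Building the SD of change from Table 1, power for 0.55 lies between 32% and 80% for correlations from 0 to 0.8, so it falls short of 80% unless the correlation reaches about 0.8. Low power for a difference of that size is therefore likely, but no single figure is established.

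**What to change.** Keep 32 patients and rewrite the paragraph:

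- Name one primary outcome, with its unit, in the same terms under Sample Size and Statistical Analysis.
- State the target between-group difference on that scale and the reason for it.
- State how the SD was derived for that same outcome. If it is an SD of change, give the assumed correlation.
- Present the calculation as a two-sided two-sample one: 14 evaluable per group give 80% power for a standardised difference of 1.10.
- On the chosen scale, and over a stated range of SDs, give the corresponding detectable difference, the power at smaller differences, and the expected 95% confidence interval half-width (about 0.78 SD).

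The value 0.71 and the Nm/kg scale should not be carried into the new text unless they are shown to belong to the chosen outcome.

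The cost is a wording change and a less favourable power statement. No extra patients are needed.
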